### Data analysis

Following the CONSORT guidelines,^
37
^ a flowchart outlining participants’ progression throughout the study will be created. This will include information on sample size, reasons for exclusions, and participant dropouts.

Data analysis will be performed by the research team, with preliminary steps including verification of data discrepancies, potential biases, anomalies, incomplete or missing data, as well as assessments of distribution normality, linearity, and homoscedasticity. These steps ensure compliance with prerequisites for subsequent statistical analyses.

Demographic and professional characteristics of participants will be analysed using descriptive statistics. This will involve measures of central tendency, variance metrics, frequency charts, and 95% confidence intervals for all subgroups.

The analysis will include group comparison tests appropriate for the type of variable under study. A univariate analysis will assess each variable before and after the intervention. Bivariate analyses will examine correlations between dependent and independent variables, while multivariate analyses will explore interactions and relationships among them.

Primary outcomes will focus on participants’ perceptions of the NPE and safety climate in primary healthcare settings. The Student’s *t*-test will be used to compare group mean values, and the paired *t*-test will examine changes within groups. Effect size interpretations will use Cohen’s D index, categorised as small (0.2–0.49), moderate (0.5–0.8), or large (>0.8).^
41
^

Multivariate analysis will include linear regression for dependent variables such as nurses' perceptions of the practice environment and safety climate in primary health care. If assumptions of normality, homoscedasticity, and variable independence are not met, variable transformation will be considered. After regression analysis, the adequacy of the model in representing the observed data will be evaluated, along with the possibility of changes in variable effects.^
42
^

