### Sample size

Considering the study’s objective, we calculated the sample size using G*Power software (version 3.1.9.6) with a two-tailed test to compare two dependent means (Student’s *t*-test). The parameters used included an effect size of 0.5, a significance level (α) of 0.05, and a statistical power (1-β) of 0.80. The calculation suggests a minimum total sample size of 34 participants (17 participants per group). The allocation ratio between the groups will be 1:1. Thus, we aim to recruit at least 34 nurses working in primary healthcare units who are interested in and agree to participate in the study.

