### Allocation, randomisation, and blinding

Participants will be allocated into two groups (intervention and control) and stratified randomisation will be performed to ensure homogeneity between the groups (1:1). Stratification will consider participants’ self-assigned codes along with sociodemographic and professional characteristics such as sex, age, educational background, professional category, total professional experience, experience in primary health care, and the type of unit where they work. Stratified randomisation will be executed using RANDOM.ORG by an independent researcher uninvolved in the PPAPEP intervention or data analysis, because it offers true random numbers that are for many purposes better than the pseudo-random number algorithms typically used in traditional computer statistical software. Regarding the randomisation during each evaluation point, questionnaires will be completed by participants, sealed in opaque envelopes labelled with the respective evaluation moment ('EM0', 'EM1', 'EM2, or 'EM3'). After the final evaluation moment ('EM3'), the questionnaires will be selected based on the administration timeline illustrated in Figure 1. This approach enables participants to choose their preferred day and time for sessions without compromising group homogeneity or randomisation. It also minimises selection and information bias by ensuring that neither the researcher nor the participants are aware of their allocation until data collection is complete. Assessments during the intervention were conducted using self-administered questionnaires, and participants were instructed not to share session information with others.

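### Allocation is stratified, but the named between-arm test is a plain t-test; if a few prognostic factors really balance the arms, that test is conservative and loses precision

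*Protocol article*

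**What the plan says.** In the Protocol article, the section on allocation, randomisation and blinding states that "stratified randomisation will be performed to ensure homogeneity between the groups (1:1" ratio). The factors are participants' "self-assigned codes along with sociodemographic and professional characteristics", the latter being "sex, age, educational background, professional category, total professional experience, experience in primary health care, and the type of unit where they work". It gives no number of levels, cut-points or block size.

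Under Data analysis, the primary outcomes are perceptions of the practice environment and of the safety climate. The Student's t-test "will be used to compare group mean values", and a paired t-test "will examine changes within groups". No stratum or covariate is attached to either test. The section later adds: "Multivariate analysis will include linear regression for dependent variables", meaning the same two outcomes. It does not say that this regression contains the arm or the stratification factors, or that it is the primary comparison.

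The Sample size section uses G*Power "with a two-tailed test to compare two dependent means", with "an effect size of 0.5, a significance level (α) of 0.05, and a statistical power (1-β) of 0.80". The result is 34 nurses, 17 per group, with no credit taken for stratification.

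**The concern.** The analysis should reflect the way the arms were formed. When allocation is balanced within strata that predict the outcome, the differences between strata no longer contribute to the sampling variation of the arm difference. The two-sample t-test still counts them as error. Its standard error then exceeds the true one, the interval is too wide, and the test rejects less often than its nominal 5%.

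What is at stake is precision. The error is in the conservative direction, so there is no added false-positive risk. With 17 nurses per arm, though, precision is scarce, and the loss is avoidable if the strata are few and prognostic.

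**Working it through.** **Inputs from the protocol.** 34 nurses, 1:1, two-sided alpha 0.05, effect size 0.5 (Sample size); seven stratification characteristics plus self-assigned codes (Allocation, randomisation, and blinding); plain t-test between arms (Data analysis).

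**Assumptions, because the protocol gives no figures.** Binary factors, equally prognostic, jointly explaining a share R² of outcome variance; permuted blocks of two within each stratum.

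**Step 1: the plan's own figure.** Noncentral-t power for a paired test at effect size 0.5 gives n = 33.4, so 34, with power 0.808. The stated 34 is reproduced, but as 34 pairs. The two-sample t-test at 0.5 needs 64 per arm (128 in total). With 17 per arm its power is 0.29.

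**Step 2: the mechanism.** With perfect balance on factors explaining R²:

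- reported SE / true SE ≈ 1/√(1 − R²)
- actual type I error ≈ P(|t₃₂| > 2.037 × that ratio)

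R² = 0.1: ratio 1/√0.9 = 1.054, cut-off 2.147, type I error 3.9%.

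R² = 0.3: ratio 1/√0.7 = 1.195, cut-off 2.435, type I error 2.1%.

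**Step 3: simulation.** 34 nurses, about 6,000 trials per setting; Monte Carlo error is about 0.6 points on power and 0.3 points on type I error. The t-test is compared with a linear regression on arm plus all k factors. Power is at a standardised difference of 0.5.

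| Factors k | R² | t-test type I | t-test power | adjusted power |
|---|---|---|---|---|
| 1 | 0 | 0.052 | 0.289 | 0.288 |
| 1 | 0.1 | 0.038 | 0.286 | 0.321 |
| 1 | 0.3 | 0.020 | 0.257 | 0.396 |
| 2 | 0 | 0.052 | 0.304 | 0.302 |
| 2 | 0.1 | 0.040 | 0.276 | 0.310 |
| 2 | 0.3 | 0.024 | 0.255 | 0.389 |
| 3 | 0 | 0.051 | 0.293 | 0.287 |
| 3 | 0.1 | 0.037 | 0.291 | 0.314 |
| 3 | 0.3 | 0.021 | 0.263 | 0.396 |
| 7 | 0 | 0.047 | 0.293 | 0.250 |
| 7 | 0.1 | 0.045 | 0.282 | 0.256 |
| 7 | 0.3 | 0.045 | 0.285 | 0.327 |
| 7 | 0.5 | 0.038 | 0.278 | 0.434 |

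For one to three factors the simulation agrees with step 2. Across those settings the adjusted model's own type I error was 4.6% to 6.0%. A separate simulation with four near-equal strata gave a t-test type I error of 4.3% at R² = 0.1, which sets the upper end of the 2% to 4.5% range.

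**Step 4: why seven factors behave differently.** Seven binary factors make 2⁷ = 128 cells. If cells are equally likely, 34 nurses occupy about 128 × [1 − (127/128)³⁴] = 30 of them, and (127/128)³³ = 77% of nurses are alone in their cell. Such strata balance almost nothing. The simulated ratio of reported to true SE is:

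- R² = 0.1: 0.343/0.339 = 1.01
- R² = 0.3: 0.344/0.336 = 1.02
- R² = 0.5: 0.345/0.329 = 1.05

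With one factor and R² = 0.3 it is 0.342/0.286 = 1.20.

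**Step 5: cost in degrees of freedom.** The t-test has 34 − 2 = 32. Two or three binary terms leave 30 or 29, and seven leave 25. With one binary and six three-level factors (1 + 6 × 2 = 13 terms) 19 remain. In that last setting, at R² = 0 to 0.3 and 4,000 runs each, adjusted power was 0.19 to 0.25 against 0.28 to 0.29 for the t-test, whose type I error stayed near 5%.

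**The case against.** The strongest case against is that the protocol lists seven factors, not two or three. Taken literally and fully crossed, they produce mostly single-person cells, so the t-test keeps close to its nominal level and adjusting for everything can be worse than doing nothing. If the personal code is literally a stratum, every stratum holds one person and the overstatement vanishes. This stands. It limits both the size of the concern and the form of the remedy.

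The gain also depends on prognostic strength, which the protocol does not give. The abstract speaks of comparing changes. If change scores are tested, stable differences by sex, age or type of unit largely cancel and R² would be lower. This stands as a reason for the lower end of the range.

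The planned linear regression could carry the adjustment, and an article may leave its covariates to an analysis plan that is not shown. This stands only in part. The article does name the test that compares the arms, and that test has no strata.

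The timing of allocation is unsettled. Table 2 puts it at the baseline evaluation, whereas the allocation section selects questionnaires after the last evaluation and lets nurses choose session times. Until these are reconciled, what the strata balance cannot be stated firmly.

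A reader might infer two stronger claims. One is that the standard error is certainly too large. The documents do not support this, because it requires prognostic factors and effective balance, and neither is shown. The other is that the trial gives up power it had secured through stratification. The sample size takes no such credit, so there is no basis for that either.

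**Conclusion.** The mismatch between stratified allocation and an unstratified primary comparison is real, and its consequence is conditional. With one to three effective binary factors and R² of 0.1 to 0.3, the t-test's type I error is about 2% to 4.5%. Its power at 0.5 is about 25% to 30%, where adjustment gives about 30% to 40%. At R² = 0 adjusting for that few factors costs almost nothing. With all seven factors crossed, type I error is about 4% to 5%. Full adjustment then loses power if the factors are weak (0.29 to 0.25 at R² = 0) and gains only if they are fairly prognostic (0.29 to 0.33 at R² = 0.3). R², the number of levels and the block size are assumptions throughout.

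The point is worth acting on because the change is cheap, but it does not threaten validity. Nor does adjustment bring the trial to 80% power. The plan's figure belongs to a paired test, two arms of 17 have about 29% at 0.5, and that sizing problem is larger and separate.

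**What to change.** In the Data analysis section, make the primary between-arm test for each outcome a linear model with arm plus a small pre-specified set, about two or three, of the stratification factors actually used in the allocation list. Choose them as the most prognostic, and fix the choice before unblinding. Report the adjusted arm difference with its 95% confidence interval, and keep the unadjusted t-test as supportive. Do not enter all seven factors. State which factors, with which categories, the list uses, and reconcile the timing of allocation between Table 2 and the allocation section so that they can be identified.

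The cost is wording only. Table 2 has the demographic and professional data collected before allocation, so no new data are needed. Two or three binary terms use 2 or 3 of the 32 degrees of freedom; factors with more levels use more. If the chosen factors turn out weak, there is little gain.

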### Data security and management

Questionnaires will remain anonymous, and data analysed in aggregate form and access restricted to the research team. Each participant will create a unique and confidential code to link pre- and post-intervention responses, ensuring anonymity. The research team will securely store the database with password protection, accessible only to investigators.

### Test monitoring

All assessment instruments used for participant evaluation have been translated and validated for the study population. Pretest questionnaires were administered to nurses to identify and address potential errors or inaccuracies and to evaluate response times.

## Discussion

### Summary

The study evaluates a training intervention for primary healthcare nurses using a rigorous methodological design. Given the scarcity of clinical trials in this area, the intervention is expected to empower professionals, encourage reflection on the work environment, and improve their wellbeing. In addition to providing evidence of the programme’s effectiveness, the study aims to guide institutional policies, inspire future research, and contribute to healthier work environments, positively impacting job satisfaction, professional retention, and the quality of patient care.

### Strengths and limitations

Results from this study will be reported in accordance with CONSORT guidelines and disseminated through peer-reviewed scientific journals and conferences focused on this field. Despite efforts to minimise bias, it is possible that nurses expressing interest in this training programme already have prior awareness of the topic, potentially influencing their perceptions of the NPE and patient safety (this may represent some level of performance bias). Some participants may be unable to attend all sessions owing to professional or personal reasons; to prevent this bias (dropout bias), sessions will be offered on two different days and at varied times. This study marks a significant advancement in the exploration of NPE, not only by analysing the outcomes of a training intervention for primary healthcare nurses, but also through its rigorous study design.

### Implication for research and practice

This study aims to provide robust evidence of the programme’s effectiveness in fostering positive NPE, informing institutional strategies, guiding evidence-based policies development, and inspiring future research for healthier, more supportive, and productive workplaces. These outcomes may enhance not only nurses’ professional satisfaction, but also retention and the quality and safety of patient care.
